# Effectiveness of an evidence-based care pathway to improve mobility and participation in older patients with vertigo and balance disorders in primary care (MobilE-PHY2): study protocol for a multicentre cluster-randomised controlled trial

**DOI:** 10.1186/s13063-022-07017-x

**Published:** 2023-02-06

**Keywords:** Dizziness, Vertigo, Balance disorder, Complex intervention, Primary care, Care pathway, Multicentre cluster randomised controlled trial, Mobility, Physiotherapy

## Abstract

**Background:**

Vertigo, dizziness or balance disorders (VDB) are common leading symptoms in older people, which can have a negative impact on their mobility and participation in daily live, yet, diagnosis is challenging and specific treatment is often insufficient. An evidence-based, multidisciplinary care pathway (CPW) in primary care was developed and pilot tested in a previous study. The aim of the present study is to evaluate the effectiveness and safety of the CPW in terms of improving mobility and participation in community-dwelling older people with VDB in primary care.

**Methods:**

For this multicentre cluster randomised controlled clinic trial, general practitioners (GP) will be recruited in two regions of Germany. A total of 120 patients over 60 years old with VDB will be included. The intervention is an algorithmized CPW. GPs receive a checklist for standardise clinical decision making regarding diagnostic screening and treatment of VDB. Physiotherapists (PT) receive a decision tree for evidence-based physiotherapeutic clinical reasoning and treatment of VDB. Implementation strategies comprises educational trainings as well as a workshop to give a platform for exchange for the GPs and PTs, an information meeting and a pocket card for home care nurses and informal caregivers and telephone peer counselling to give all participants the capability, opportunity and the motivation to apply the intervention. In order to ensure an optimised usual care in the control group, GPs get an information meeting addressing the national guideline. The primary outcome is the impact of VDB on participation and mobility of patients after 6 month follow-up, assessed using the Dizziness Handicap Inventory (DHI) questionnaire. Secondary outcomes are physical activity, static and dynamic balance, falls and fear of falling as well as quality of life. We will also evaluate safety and health economic aspects of the intervention. Behavioural changes of the participants as well as barriers, facilitating factors and mechanisms of impact of the implementation will be investigated with a comprehensive process evaluation in a mixed-methods design.

**Discussion:**

With our results, we aim to improve evidence-based health care of community-dwelling older people with VDB in primary care.

**Trial registration:**

DRKS, DRKS00028524 retrospectively registered on March 24, 2022.

**Supplementary Information:**

The online version contains supplementary material available at 10.1186/s13063-022-07017-x.

## Background

Vertigo, dizziness and balance disorders (VDB) are common leading symptoms in older patients and can be caused by various conditions [1, 2]. The prevalence is about 20% in people over 60 and 30% in people over 70 and increases with age [1, 3, 4]. Cases of VDB are among the 20 most common reasons for encounter in general practitioners’ (GP) practice in Germany [5, 6] and can have a highly disabling impact on the daily lives of older adults and are associated with gait abnormalities, an increased risk of falls, social withdrawal, limitations in autonomy [1, 7, 8], depression and reduced functional ability [9–12]. In primary care, the diagnosis of VDB is often inadequate, the according management partly ineffective or insufficient [13–16]. Current treatment approaches include patient education, pharmaceutical therapy, medication review and physiotherapy (PT) [17]. Recent evaluations indicate that physiotherapy in particular can have a beneficial impact on balance and fall risk for many patients with VDB [2, 18–23]. Despite that, the current clinical guideline for German primary care practitioners recommends the prescription of physiotherapy for patients with acute dizziness only in fairly limited cases [17].

To improve primary care of community-dwelling older patients with VDB, we developed and piloted an evidence-based, multidisciplinary care pathway (CPW) [24–26]. Findings from the pilot study indicate that benefits for patients are possible, both GPs and PTs were satisfied with the educational trainings and patients responded well to the physiotherapy. However, recruitment was challenging.

## Methods

This study protocol follows the Standard Protocol Items: Recommendations for Interventional Trials (SPIRIT) Checklist [27] for Trials. The whole project is structured according to the UK Medical Research Council guidance for development and evaluation of complex interventions [28]. In the previous study, we covered the two steps ‘Development and Feasibility/ Piloting’ [24, 25]. In the current study, we proceed with the step, ‘Evaluation’.

The study is designed as a pragmatic, controlled, multicentre, cluster-randomised, cluster blinded, trial with two parallel groups and a 1:1 allocation and takes place in two regions in Germany: South-eastern Bavaria and Saxony. Both sites have an urban centre with a rural environment.

### Objectives

#### Primary objective

The main objective of the present study is to evaluate the effectiveness and safety of the CPW in terms of improving mobility and participation in community-dwelling older people with VDB in primary care in comparison to a control group, which receives optimised usual care. The impact of VDB on mobility and participation will be assessed by the Dizziness Handicap Inventory (DHI) questionnaire [29] as primary outcome.

#### Secondary objectives

Secondary outcomes are physical activity, static and dynamic balance, falls and fear of falling as well as quality of life. We will also evaluate the safety in terms of falls. Cost-effectiveness and cost-utility of the CPW will be assessed in a health economic evaluation alongside the trial. To understand the behaviour change process, as well as barriers and facilitating aspects of implementation, the study will be accompanied by a comprehensive process evaluation.

### Eligibility criteria

#### Patients

Primary target population are community-dwelling older patients aged at least 60 years, who consulted their GP with recent or chronic complaints of VDB. They should be able to stand up on their own and stand for two minutes with support.

Exclusion criteria for patients are:Not able to give written informed consent,A DHI less than 12 points [30]. A DHI of at least 12 points is required, since the suggested minimal clinical important difference is 12 points [30] and patients with a lower DHI score are not at risk to reach the effectiveness threshold.Moderate to severe cognitive impairments as defined by the Mini-Mental State Examination of less than 20 points [31],The presence of psychiatric disorders identified by International Statistical Classification of Diseases and Related Health Problems (ICD) codes (F10.-F19, F20.-F29, F30., F31., F32.2, F32.3, F32.8, F32.9, F33.2, F33.3, F33.8, F33.9),Limited life expectancy (≤ 1 year) due to an advanced disease with a poor prognosis estimated by GP,VDB caused by current substance abuse,Unable to complete questionnaires and follow instructions because of insufficient command of the German language.

#### Health professionals

Participating GP practices, PT practices and home care nursing services are required to have an accreditation of the German statutory health insurance. GP practices with practice software that is not eligible for identification patients as potential study participants will be excluded.

### Sample size

Sample size calculation was informed by data of a cohort study with the same population [32]. Data gave evidence of an ICC = 0.04 and an expected standard deviation of 25. A cluster size of 10 is assumed, i.e. the variance inflation factor is 1 + (10 − 1) × 0.04 = 1.36. The study plans to detect a score difference between intervention groups of at least 12 points [30] on a two-sided alpha level of 0.05 with a power of 80%, resulting in a total sample size of ((1.96 + 0.84)^2^ × 2 × 25^2^ × 1.36)/12^2^ = 92.6. Recruitment of 12 clusters à 10 patients accounts for a dropout rate of 23%. The study will be conducted in two waves, resulting in six clusters (three per study centre) à ten patients being recruited per wave. Current experience shows that a few clusters will possibly fail to recruit the necessary number of patients. In this case, we will recruit more patients in other clusters to compensate for this. To maintain the statistical power of the study, the following rule will be applied: number of patients to be additionally recruited in other clusters = 1.5 × number of patients that some clusters fail to recruit.

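### The sample-size formula gives the number per group but is labelled the total; on the stated inputs the trial has about 51% power, not 80%

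*Protocol article*

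**What the plan says.** All references are to the protocol article.

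- Sample size, target: "The study plans to detect a score difference between intervention groups of at least 12 points".
- Sample size, variance inputs: "Data gave evidence of an ICC = 0.04 and an expected standard deviation of 25".
- Sample size, clustering: "A cluster size of 10 is assumed, i.e. the variance inflation factor is" 1.36.
- Sample size, result: the calculation is made "on a two-sided alpha level of 0.05 with a power of 80%, resulting in a total sample size of" ((1.96 + 0.84)² × 2 × 25² × 1.36)/12² = 92.6.
- Sample size, recruitment: 12 clusters of 10 "patients accounts for a dropout rate of 23" per cent.
- Abstract, Methods: "A total of 120 patients over 60 years old with VDB will be included".
- Methods, opening section: two parallel groups, allocated 1:1.
- Data analysis: a linear mixed model of the DHI change from t0 to t2, with group and initial DHI as fixed factors and a random intercept for cluster. Inference is by a Wald t-test, and the last observation is carried forward for dropouts.

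**The concern.** The difference between two group means, with n patients in each group, has variance 2 × SD²/n before clustering. Solving for n puts a 2 in the numerator, and that n is the size of one group. A formula for the total under 1:1 allocation carries a 4. The protocol uses the 2 and calls the result the total.

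This goes beyond wording, because the recruitment target of 120 rests on the mislabelled figure. The stated 80% power applies to the primary outcome, at the difference the protocol itself treats as clinically meaningful. If true power is near one half, a real 12-point benefit would be missed about half the time, while readers are told the risk is 20%. A null result could then be read as evidence of no effect. The same section also has a rule for replacing shortfalls in recruitment, meant to preserve the study's power; that rule protects a power which the calculation does not deliver.

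**Working it through.** **Inputs (Sample size section).** Two-sided alpha 0.05 (z = 1.96), power 80% (z = 0.84), difference 12, SD 25, ICC 0.04, cluster size 10, 12 clusters, 23% dropout.

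**1. The plan's own figure**

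- Design effect: 1 + 9 × 0.04 = 1.36.
- (1.96 + 0.84)² = 7.84.
- 7.84 × 2 × 625 × 1.36 / 144 = 92.56, which matches the stated 92.6.
- Dropout: 1 − 92.6/120 = 22.8%, which matches the stated 23%. So 120 was built on 92.6 as the total for both groups.

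**2. What the figure is**

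n per group = (z_α + z_β)² × 2 × SD² × DE / δ² = 92.56.

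- Total: 2 × 92.56 = 185.1.
- With 23% dropout: 185.1 / 0.77 = 240.4, or about 24 clusters of 10, against 120 patients in 12 clusters planned.

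No simple variant makes 92.6 a total. With the factor 4, a one-sided 0.05 test gives 146.0, and a two-sided test without the design effect gives 136.3.

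**3. Power of the planned size**

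SE = √(4 × SD² × DE / N), with N the total analysed. Power ≈ Φ(12/SE − 1.96). Detectable difference at 80% power = 2.80 × SE.

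| N analysed | SE | 12/SE | Power, normal | Power, t on 10 df | Detectable difference (normal) |
|---|---|---|---|---|---|
| 92.6 | 6.06 | 1.98 | 50.8% | 43.3% | 17.0 |
| 120 | 5.32 | 2.25 | 61.6% | 53.0% | 14.9 |
| 185.2 | 4.28 | 2.80 | 80.0% | – | 12.0 |

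The t column uses 12 clusters − 2 = 10 degrees of freedom and the noncentral t distribution. It is a sensitivity figure: it shows how few practices carry the treatment comparison.

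If dropout also shrinks the mean cluster size to 92.6/12 = 7.7, the design effect is 1 + 6.7 × 0.04 = 1.27, and power at 92.6 is 53.6% (normal).

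**4. Could baseline adjustment restore 80%?**

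The correlation r between baseline and t2 DHI is not in the document, so every value below is an assumption.

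*If 25 is the SD of a single score*, adjustment multiplies the variance by 1 − r². Power is shown as normal / t on 10 df:

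| r | N = 92.6 | N = 120 |
|---|---|---|
| 0.3 | 55% / 47% | 66% / 57% |
| 0.5 | 63% / 54% | 74% / 65% |
| 0.6 | 70% / 61% | 80% / 72% |
| 0.7 | 79% / 71% | 88% / 81% |

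The r needed for 80% is about 0.71 (normal) or 0.77 (t) at 92.6, and about 0.59 or 0.69 at 120.

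*If 25 is the SD of the change*, with equal variances at both times, the residual variance after adjustment is 625 × (1 + r)/2. At r = 0 this is half of 625, which gives 80% at 92.6 (normal). Any positive r gives less, for example 63% at r = 0.5. With all 120 analysed, 80% needs r of about 0.29 or less.

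**The case against.** The labelling error itself has no defence in the document. The case on the other side concerns its consequences.

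- **All 120 may be analysed.** The Data analysis section specifies intention to treat with last observation carried forward, so dropouts stay in the model and 62% may be the fairer figure. This stands as an upper case on the stated inputs. It is still far below 80%, and a carried-forward baseline value tends to dilute a treatment effect. The 51% is the direct counterpart of the plan's claim, because the plan attaches 80% to 92.6 patients.
- **The primary model adjusts for initial DHI.** An unadjusted calculation may understate its power. This also stands in part: with a correlation of about 0.6 and all 120 analysed, power reaches 80% under the normal approximation. But the sample-size formula has no correlation term, no correlation is reported, and the document does not say whether 25 is the SD of the score or of the change. The power of the adjusted model cannot be fixed from the document, and an unstated assumption cannot justify the printed total.
- **Degrees of freedom are a matter for the analysis plan.** Normal quantiles are a common approximation, and a t-test is already specified. The t figures are therefore supporting information and not a second error.

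**Conclusion.** The point holds: the sample-size statement is wrong as written. The 92.6 is the number per group; the total on the protocol's own inputs is about 185 analysable, or about 240 recruited, twice what is planned.

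The plan's 80% becomes about 51% for a 12-point difference, or about 43% with t on 10 df. With all 120 analysed it is about 62%, or 53% with t. These figures rest on SD 25, ICC 0.04, clusters of 10 and no gain from baseline adjustment, which is the basis the protocol itself used. Adjustment might close the gap, but only under correlations the document does not state.

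**What to change.** Correct the Sample size section as follows:

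1. State that 92.6 is per group, so the total is 186 when rounded up to equal groups (2 × 93), or about 240 with 23% dropout.
2. Restate what the planned 12 × 10 design delivers on the stated inputs: about 51% power for 12 points at 92.6 analysable patients (about 43% with t on 10 df), or a detectable difference of about 17 points. Give the figures for all 120 alongside.
3. If the sponsor relies on baseline adjustment, state whether 25 is the SD of the score or of the change, the baseline–t2 correlation from the cohort or pilot data, and the resulting power with t quantiles on 10 df.

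The target of 120 in the abstract can stand as the recruitment number, but it should no longer be tied to 80% power on the present calculation. The change is to wording only and needs no additional patients. Its cost is that the stated power becomes less favourable, and a non-significant result will have to be interpreted with that in view.

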### Data analysis

The data analysis of the measured outcomes will be done by a blinded biostatistician who is not involved in the study. The primary analysis will be based on a linear mixed model of the DHI changes between t_0_ and t_2_, using intervention group and initial DHI as fixed factors and a random intercept for cluster. The statistical inference will be based on the Wald *t*-test for the intervention on an alpha level of 5% (two-sided). Similar models will be applied for exploratory analyses of the secondary outcomes. No pre-specified subgroup analyses are planned. Due to the restricted sample size, no additional adjustments for other fixed effects are planned. Range and cross-checks of the outcome variables and key baseline patient characteristics will be performed. Impossible or implausible data will trigger queries to the team of the principal investigator. All analyses will be based on the intention-to-treat principle. In case of dropouts, the last available observation will be carried forward. No interim analyses are planned.

For the process evaluation, quantitative data will be analysed descriptively. Qualitative data from interviews and field notes from research team, GPs and PTs will be analysed with content analysis [50], which will be performed by two independent researchers from the study centres.

To analyse the cost-effectiveness of the intervention, an incremental cost-effectiveness ratio and an incremental cost-utility ratio will be calculated as the ratio of the difference in mean cost and the difference in mean health effects (DHI or QALY) between study groups during the 6-month follow-up period. Non-parametric bootstrap method will be employed to generate confidence intervals around the difference in mean cost and the difference in mean health effects. Uncertainty surrounding the cost-effectiveness ratio and cost-utility ratio will be presented on the cost-effectiveness plane. Furthermore, cost-effectiveness acceptability curves, based on the incremental net-monetary benefit will be constructed. The study will be terminated when all collected data have been analysed and utilised within the analysis plan.

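### The sample size uses normal quantiles although the planned t-test rests on 12 practices; this alone costs about 7.5 to 8.6 points of power, on top of a per-arm number labelled as a total

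*Protocol article*

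**What the plan says.** All references are to the protocol article.

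- **Sample size, inputs.** Variability comes from an earlier cohort: "Data gave evidence of an ICC = 0.04 and an expected standard deviation of 25". On practice size the section says "A cluster size of 10 is assumed", which gives the inflation factor 1 + 9 × 0.04 = 1.36. The target is worded "The study plans to detect a score difference between intervention groups of at least 12 points", and the error rates are set as "on a two-sided alpha level of 0.05 with a power of 80" per cent.
- **Sample size, formula.** The calculation reads "resulting in a total sample size of ((1.96 + 0.84" and so on, ending at 92.6. The recruitment target is then explained: "Recruitment of 12 clusters à 10 patients accounts for a dropout rate of 23" per cent.
- **Methods and Allocation.** The design is a cluster-randomised "trial with two parallel groups and a 1:1 allocation". GP practices are the units randomised, in blocks of two within region, so the 12 practices split 6 and 6.
- **Data analysis.** The primary analysis is a linear mixed model for the change in DHI, with fixed effects for arm and baseline score and a random practice effect. On the test it says: "The statistical inference will be based on the Wald *t*-test for the intervention on an alpha level of 5% (two-sided"). No method for the degrees of freedom is named.

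**The concern.** The inflation factor enlarges the variance of the estimated difference to allow for clustering. It does not allow for that variance having to be estimated from only 12 practices. The formula treats the variance as known (1.96), while the planned test is a t-test of a factor that varies only between practices. The size calculation and the test therefore use different reference distributions.

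The 80% is a printed figure, and the result will be read against it. If true power is well below 80%, a null result could be over-read as evidence against a 12-point effect. If the analysis instead used a normal reference to match the formula, the two-sided 5% level would be exceeded.

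**Working it through.** **Inputs (Sample size section):** difference 12, SD 25, ICC 0.04, cluster size 10, two-sided alpha 0.05, 12 practices, 120 patients recruited, 92.6 needed.

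**1. The printed figure.** (1.96 + 0.84)² × 2 × 25² × 1.36 / 12² = 92.56, which is the printed 92.6. Dropout: 1 − 92.6/120 = 22.8%, the printed 23%. The arithmetic is right. But with the factor 2 × SD² this is the standard formula for the number per arm; the total on the same inputs is 2 × 92.56 = 185.1.

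**2. Standard error for 12 practices of 10.** The estimate is a difference between two means of 6 practice means each. One practice mean has variance 25² × 1.36 / 10 = 85. The difference has variance 85 × 2/6 = 28.33, so SE = 5.323. The same follows from 25 × √(4 × 1.36 / 120).

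**3. Reference distribution.** With equal practice sizes this variance is estimated by the between-practice mean square, on 12 − 2 = 10 degrees of freedom. The two-sided 5% critical value is 2.228.

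**4. Power.** Non-centrality = 12 / SE. Normal power = Φ(non-centrality − 1.96). The t power comes from the non-central t with 10 df.

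| Setting | SE | Non-centrality | Normal | t, 10 df | Loss (points) |
|---|---|---|---|---|---|
| 120 patients, factor 1.36 | 5.323 | 2.254 | 61.6% | 53.0% | 8.5 |
| 92.6 in total, factor 1.36 | 6.059 | 1.980 | 50.8% | 43.3% | 7.5 |
| 92.6 in total, 7.7 per practice, factor 1.27 | 5.852 | 2.050 | 53.6% | 45.8% | 7.8 |
| Non-centrality assumed by the formula | – | 2.80 | 80.0% | 71.4% | 8.6 |

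In the third row 92.6/12 = 7.7 patients per practice, and 1 + 6.7 × 0.04 = 1.27. The last row isolates the quantile effect and does not describe this trial: non-centrality 2.80 needs about 185 patients at SD 25 and factor 1.36.

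**5. Does the test keep 5% if 1.96 is used?** Two simulations of 6 + 6 practices of 10 (ICC 0.04, effect scaled to non-centrality 2.80, practice variance truncated at zero) agree. Using 1.96 gave about 78% power with a type I error of 5.9% to 6.0%. Referring the same statistic to t with 10 df gave about 70% power, and the plain between-practice t-test 71% to 72%. The normal reference keeps most of the power only by exceeding the stated level.

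**The case against.** **Degrees of freedom.** The protocol names no method, and the choice may sit in an analysis plan that is not shown. A reader might infer that every method gives about 10. That is too strong. With ICC 0.04 and 12 practices of 10, the practice variance is estimated as zero in about 28% of trials (probability that F with 10 and 108 df falls below 0.96/1.36 = 0.706), and software may then assign far larger degrees of freedom. At non-centrality 2.80, 20 df would give 76% and 107 df 79%. This stands as a limit on the size of the loss. It does not rescue the 80%: a normal or patient-level reference used throughout would exceed 5%, and even the normal formula gives only 62% with 120 patients.

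**Accepting 92.6 as a total.** If non-centrality were 2.80 at 92.6 patients in total, all 120 would give 2.80 × √(120/92.6) = 3.19 and t(10) power of about 82%. The last-observation-carried-forward rule does keep dropouts in the analysis set. But that reading needs an SD of √(92.6 × 144 / (4 × 7.84 × 1.36)) = 17.7, and the protocol states 25.

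**Adjustment for initial DHI.** The protocol does not say whether 25 is the SD of the score, the change or the residual. If it is an unadjusted score SD and the baseline correlation were 0.6 (an assumption), the residual SD would be 25 × √(1 − 0.36) = 20, and 120 patients would have 80.5% by the normal formula and 71.9% by t(10). At 0.7 these would be 88.4% and 81.1%. The point is fair, but the protocol gives no correlation and claims no such gain.

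**Common practice.** Normal quantiles with a design effect are a usual planning approximation, and the printed arithmetic is correct. That is conceded; with only 12 practices, however, the approximation is not harmless.

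**Conclusion.** The concern holds as one component of an overstated power. Normal quantiles in place of t with about 10 df account for 7.5 to 8.6 points. The larger component is the per-arm number labelled as a total. Together they put power at about 53% with 120 patients and about 43% to 46% with 92.6 analysed, some 27 to 37 points below the stated 80%.

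A reader might infer that the stated power is wrong by only 8 to 9 points and that the trial has 71%. The protocol does not support this: 71% pairs the information of about 185 patients with the degrees of freedom of 12 practices of 10, and no version of the trial on its stated inputs has both.

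The figures assume SD 25 as the analysis SD (as the formula uses it), ICC 0.04, equal practice sizes, and a between-practice reference with 10 df.

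**What to change.** In the Sample size section, recompute power with the t distribution on (practices − 2) degrees of freedom, matching the planned Wald t-test. For the 12-practice design, replace 80% by about 53% (120 patients) and about 43% to 46% (92.6 patients), saying whether the inflation factor is kept at 1.36 or recalculated for 7.7 patients per practice. Correct the label on 92.6 at the same time. Do not print 71% as this trial's power. If adjustment for initial DHI is credited, state the assumed correlation and the residual SD.

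The cost is a few lines of recalculation. No extra recruitment is proposed; the only downside is a less favourable stated power.
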